## Abstract

**Background:**

Osteoarthritis of the hip is successfully treated by total hip arthroplasty with metal-on-polyethylene articulation. Polyethylene wear debris can however lead to osteolysis, aseptic loosening and failure of the implant. Large head metal-on-metal total hip arthroplasty may overcome polyethylene wear induced prosthetic failure, but can increase systemic cobalt and chromium ion concentrations. The objective of this study is to compare two cementless total hip arthroplasties: a conventional 28 mm metal-on-polyethylene articulation and a large head metal-on-metal articulation. We hypothesize that the latter arthroplasties show less bone density loss and higher serum metal ion concentrations. We expect equal functional scores, greater range of motion, fewer dislocations, fewer periprosthetic radiolucencies and increased prosthetic survival with the metal-on-metal articulation.

**Methods:**

A randomized controlled trial will be conducted. Patients to be included suffer from non-inflammatory degenerative joint disease of the hip, are aged between 18 and 80 and are admitted for primary cementless unilateral total hip arthroplasty. Patients in the metal-on-metal group will receive a cementless titanium alloy acetabular component with a cobalt-chromium liner and a cobalt-chromium femoral head varying from 38 to 60 mm. Patients in the metal-on-polyethylene group will receive a cementless titanium alloy acetabular component with a polyethylene liner and a 28 mm cobalt-chromium femoral head. We will assess acetabular bone mineral density by dual energy x-ray absorptiometry (DEXA), serum ion concentrations of cobalt, chromium and titanium, self reported functional status (Oxford hip score), physician reported functional status and range of motion (Harris hip score), number of dislocations and prosthetic survival. Measurements will take place preoperatively, perioperatively, and postoperatively (6 weeks, 1 year, 5 years and 10 years).

**Discussion:**

Superior results of large head metal-on-metal total hip arthroplasty over conventional hip arthroplasty have been put forward by experts, case series and the industry, but to our knowledge there is no randomized controlled evidence.

**Conclusion:**

This randomized controlled study has been designed to test whether large head metal-on-metal cementless total hip arthroplasty leads to less periprosthetic bone density loss and higher serum metal ion concentrations compared to 28 mm metal-on-polyethylene cementless total hip arthroplasty.

**Trial registration:**

Netherlands Trial Registry NTR1399

## Background

Painful osteoarthritis of the hip can be successfully treated by total hip arthroplasty (THA). Conventional total hip prostheses consist of a 28 mm metal head and a polyethylene cup. Polyethylene wear debris can however lead to osteolysis, bone loss, aseptic loosening and eventually failure of the implant, especially in high demand young patients [1]. Metal-on-metal (MM) total hip arthroplasty is an alternative to overcome polyethylene wear induced prosthetic failure. The MM wear rate is reported to be 20 to 100 times lower than conventional polyethylene wear rates, roughly 6 μm per year [2]. MM wear rate is also influenced by the size of the articulation and its clearance (i.e. the difference between the radius of the head and the shell): larger heads show lower wear rates provided they have a low clearance [3]. Another advantage of larger head sizes seems to be an increased range of motion and a reduced number of dislocations [4]. The main claim of metal-on-metal articulations is a reduction of wear and a subsequent lower incidence of periprosthetic osteolysis. Since osteolysis is implicated in the early phases of prosthetic loosening and failure, it is essential to accurately quantify periprosthetic osteolysis. Conventional radiology is not sensitive and accurate enough to detect small amounts of osteolysis, but dual energy x-ray absorptiometry (DEXA) is able to detect even small defects in the periprosthetic bone in the acetabulum [5]. In spite of the advantages of low wear and fewer dislocations, metal-on-metal hip prostheses increase systemic cobalt and chromium ion concentrations [6]. The long term effects of these ions are unknown, but concerns are hypersensitivity, mutagenicity and carcinogenicity [7].

The objective of this study is to conduct a randomized controlled trial to compare two cementless total hip arthroplasties: a conventional 28 mm metal-on-polyethylene articulation and a metal-on-metal large head articulation. We hypothesize that the large head metal-on-metal arthroplasties show less bone mineral density loss and higher serum metal ion concentrations (primary outcome parameters). We expect equal functional scores, greater range of motion, less dislocations, fewer periprosthetic radiolucencies and increased prosthetic survival with the MM articulation (secondary outcome parameters). The present paper reports on the design of the study.

## Methods

### Study design

A randomized controlled trial will be conducted and concealed allocation will be used to allocate patients to either metal-on-polyethylene or metal-on-metal cementless total hip arthroplasty. The randomization procedure is based on sequentially numbered opaque sealed envelopes, produced by an external institution not involved in the selection, clinical care and evaluation of the patients. The study design, procedures and informed consent are approved by the local Medical Ethical Committee (registration number 2005–42). The trial is registered in the Netherlands Trial Registry (NTR1399). Guidelines of the Consort Statement are followed [8].

### Study population

The study will be conducted at the Department of Orthopaedic Surgery of the Martini Hospital, which is a large teaching hospital in the city of Groningen, the Netherlands. Patients to be included suffer from non-inflammatory degenerative joint disease of the hip including osteoarthritis, avascular necrosis and traumatic arthritis, are aged between 18 and 80 and are admitted for primary cementless unilateral THA. Patients with active infection, revision arthroplasty, marked bone loss, and unwillingness or inability to follow instruction are excluded. Participation in the study is voluntary and informed consent is required. The inclusion period is planned from September 2006 to September 2009.

### Intervention

#### Metal-on-metal (MM)

Patients in the metal-on-metal group will receive a metal-on-metal articulation total hip arthroplasty, a cementless plasma sprayed porous coated titanium alloy acetabular component with a cobalt-chromium liner (M2a-Magnum™, Biomet) and a cobalt-chromium femoral head with a carbon concentration between 0.20% and 0.30%. The radial clearances of the articulations vary between 17.5 and 150 micrometers. The head sizes vary from 38 to 60 mm, depending on the shell sizes which range from 44 to 66 mm. The geometry of the patient determines the largest possible shell size and head size to be implanted.

#### Metal-on-polyethylene (MP)

Patients in the metal-on-polyethylene group will receive a metal-on-polyethylene total hip arthroplasty, a cementless plasma sprayed porous coated titanium alloy acetabular component (Mallory-Head^®^, Biomet) with a polyethylene liner (ArCom™, Biomet) and a 28 mm cobalt-chromium femoral head with a carbon concentration between 0.20% and 0.30%. In both the MM and MP groups the same cementless femoral component is used: a proximally plasma sprayed porous coated titanium alloy (Ti_6_Al_4_V) stem (Mallory-Head^®^, Biomet).

According to the surgeon's preference, a posterolateral or anterolateral surgical approach in lateral decubitus position is used. Antibiotic prophylaxis with a first-generation cephalosporin will be given preoperatively and during the first twenty-four hours intravenously. All patients will be treated postoperatively following a standardized protocol, in terms of analgesia and mobilization. As prophylaxis against thrombosis, oral anticoagulation by coumarin-derivate is given 6 weeks postoperatively.

### Measurements

In this study the following outcome parameters will be assessed: bone densitometry and serum metal ion concentration (primary outcome parameters), self reported functional status, physician reported functional status, range of motion, number of dislocations, radiographic evaluation and prosthetic survival (secondary outcome parameters). Measurements will take place preoperatively, perioperatively, and postoperatively (6 weeks, 1 year, 5 years and 10 years).

#### Bone densitometry

Bone mineral density (BMD) measurements will be performed using a dual energy x-ray absorptiometry (DEXA) scanner (Hologic Inc., Bedford, Mass., United States) in order to calculate bone density changes around the acetabular component. Four horizontal regions of interest (ROI) are defined, as suggested by Wilkinson [9]. In addition, an extra ROI is defined in the os ilium to serve as control. The manufacturer's metal removal software will be used. The contralateral normal hip will be scanned following a standard manufacturer's protocol to establish BMD in the femoral neck, trochanter, intertrochanteric, total hip and Ward's triangle sites.

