#### Serum metal ion concentration

Serum ion concentrations for cobalt, chromium and titanium will be determined by venous blood sampling. Cobalt and titanium concentrations are analyzed by inductively coupled plasma mass spectrometry (ICP-MS; Agilent 7500 series, Agilent Technologies) and chromium is measured by grafite furnace atomic absorption spectrometry with Zeeman correction (GFAAS; Varian 220Z, Varian Inc.). The patients' sera may also be used to assess cytokine levels and effects of these ions on osteoblast cells.

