### Sample size

It is our hypothesis that large head metal-on-metal arthroplasties will show less bone mineral density loss and higher serum metal ion concentrations compared to the conventional 28 mm metal-on-polyethylene articulations. In order to detect a least clinical relevant difference in bone mineral density (BMD) of 0.25 g/cm^2 ^with a standard deviation of 0.4, 41 patients are needed in each group (alpha 0.05, power 0.80). Based on previous work with cemented THA we expect a drop-out rate of 10%, but we also expect conversion to cemented cups if adequate cementless fixation fails. We therefore aim to include 50 patients in each group. Comparable studies also used 50 patients in each group [15,16]. In order to detect a clinical difference of 2.5 μg/liter in serum metal ion concentration with a standard deviation of 1.8, 8 patients per group are needed (alpha 0.05, power 0.80). To compensate for patients withdrawn from the study, (the first) 15 patients will be included in each group. A comparable study used 10 patients in each group [17].

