### Statistical analysis

The Statistical Package for the Social Sciences version 14.0 for Windows (SPSS Inc.) will be used. Group comparisons are based on intention-to-treat analysis. Non-parametric tests are used for comparisons of means within groups (Wilcoxon's Signed Ranks Test) and between groups (Mann-Whitney Test) if our expectation of a skewed distribution of Oxford and Harris Hip scores postoperatively is confirmed. Chi-square (Fisher's Exact) tests are employed for analyses of categorical variables. Cumulative implant survival is calculated by Kaplan-Meier time series (Mantel-Cox log rank test). A two-sided p-value of < 0.05 is assumed to be significant.

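### Eligibility lets patients with another metal joint implant into the 15-per-arm serum ion comparison, so their ions cannot be attributed to the study bearing; the likely harm is noise and inflated levels, not systematic bias between arms

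*Protocol article*

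**What the plan says.** All references are to the protocol article.

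- **Bone densitometry** takes a normal opposite hip for granted: "The contralateral normal hip will be scanned following a standard manufacturer's protocol". The same section names a separate region in the os ilium as the control for the acetabular measurements.
- **Study population** admits patients who "are aged between 18 and 80 and are admitted for primary cementless unilateral THA". The exclusions are: "Patients with active infection, revision arthroplasty, marked bone loss, and unwillingness or inability to follow instruction are excluded". None of them concerns the opposite hip or metal implants elsewhere.
- **Measurements** lists "bone densitometry and serum metal ion concentration (primary outcome parameters") and schedules assessments before surgery and then out to 10 years.
- **Serum metal ion concentration**: "Serum ion concentrations for cobalt, chromium and titanium will be determined by venous blood sampling".
- **Sample size** bases the ion comparison on a "clinical difference of 2.5 μg/liter in serum metal ion concentration with a standard deviation of 1.8, 8 patients per group are needed" and enrols the first 15 patients in each group, with no further condition on who they are.
- **Statistical analysis** specifies intention-to-treat group comparisons and two-sided testing at 0.05.

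**The concern.** Unilateral describes the operation for which the patient is admitted. It does not say that the other hip is native. A patient who already has a prosthesis on the other side, or another cobalt, chromium or titanium joint implant, meets every stated criterion. The population has degenerative hip disease, so a second replacement during 10 years is also foreseeable.

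Serum ions are systemic, and a blood sample cannot show which implant released them. If the trial enrols exactly as written, ions from a second implant are counted as the study bearing's. This affects a primary outcome in a small group. It also affects the long-term ion levels that the Discussion says the trial will provide: those are within-arm quantities, and randomisation does not protect them.

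The criteria also do not match the densitometry section, which presumes a normal opposite hip that eligibility does not secure.

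**Working it through.** **Inputs from the article (Sample size, Statistical analysis):** difference 2.5 µg/L, SD 1.8, two-sided alpha 0.05, power 0.80, 15 per group.

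**Inputs assumed, because the article gives neither:** the proportion p of patients carrying another implant, and the amount a that each such implant adds to serum ions (1, 2.5 or 5 µg/L).

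**1. The plan's own figure.** n per group = 2 × [1.8 × (1.960 + 0.842) / 2.5]² = 8.14. The stated 8 is this value rounded down; rounding up gives 9, and the t-test version gives 9.2, so 10. The figure is reproduced closely enough for this purpose. At 15 per group, the standard error of the difference is 1.8 × √(2/15) = 0.66 µg/L and t-test power is 96%.

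**2. Effect of one carrier.** In a group of 15, one patient carrying an extra a shifts the group mean by a/15: 2.5/15 = 0.17 µg/L, or 5/15 = 0.33 µg/L.

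**3. Power with carriers.** A carrier proportion p raises the variance in that arm to 1.8² + a² × p(1 − p). If only the metal-on-polyethylene (MP) arm has carriers, the difference also falls to 2.5 − a × p. Take p = 3/15 = 0.2. For a = 2.5, the variance is 3.24 + 6.25 × 0.16 = 4.24 (SD 2.06). With carriers in both arms, the standard error is 2.06 × √(2/15) = 0.75 and the difference stays at 2.5. With carriers in the MP arm only, the pooled SD is √[(3.24 + 4.24)/2] = 1.93 and the difference is 2.0. Two-sided t-test power at 15 per group:

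| Each implant adds | Carriers in both arms (difference 2.5) | Carriers in MP only (difference) |
|---|---|---|
| none | 96% | 96% (2.5) |
| 1 µg/L | 95% | 92% (2.3) |
| 2.5 µg/L | 89% | 78% (2.0) |
| 5 µg/L | 69% | 41% (1.5) |

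Simulation of the both-arms case at p = 0.2 gives the same values (0.95, 0.89, 0.69), an average difference that stays at 2.5, and type I error near 0.05.

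**4. Chance imbalance.** With 15 per arm and carrier proportions of 10%, 20% or 30%, the two arms differ by two or more carriers with probability 35%, 49% or 55% (two independent binomial counts).

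**The case against.** **The article is condensed.** Detailed criteria and rules for later implants may sit in the full protocol. This is fair for the handling of later samples. It carries less weight for entry: the article states its eligibility list and its rule for choosing the ion subset, and followed as written they admit these patients. An analysis plan cannot undo enrolment.

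**Normal may only identify which hip is scanned.** That is possible, and this part is minor. A reader might infer that the primary bone density comparison loses its reference once the other hip is replaced. The document does not support that: the stated control is the os ilium region, and the opposite hip has no stated role in comparing the groups.

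**Randomisation and the preoperative measurement already help.** Carriers are balanced on average, so implants at entry do not bias the between-arm difference, and a raised preoperative value would be visible. This stands. It leaves added variance and chance imbalance, and a preoperative value cannot correct for an implant placed later.

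**The size is assumed.** A reader might infer that other implants systematically dilute the ion difference, with power falling to 78%. That requires carriers in the MP arm only and 2.5 µg/L from each. The article's 2.5 µg/L is a target difference between groups, not the release of another implant, and nothing suggests that carriers would gather in one arm. With carrier proportions of 5% to 30%, three or more in MP and none in metal-on-metal has a probability of only 0.4% to 4%. At 1 µg/L, power stays at 92% to 95%.

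**Cutting off samples after a later implant conflicts with intention-to-treat.** This also stands. It gains little in the balanced case: dropping three per arm leaves 12 per arm and 90% power, against 89% with all values kept.

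**Conclusion.** The point holds in a limited form. As written, eligibility and the first-15 rule allow another implant's ions to be counted as the study bearing's in a primary outcome. The expected harm is noise, chance imbalance between small groups and inflated within-arm levels, most of all at the late visits.

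Under the balanced assumption of 20% carriers, power ranges from 95% to 69% as the added amount goes from 1 to 5 µg/L. It stays above the planned 80% unless the added amount is well above 2.5 µg/L. The MP-only column shows an unfavourable scenario, not an expectation. All of these figures depend on a carrier frequency and an ion release that the document does not give. The case for a change rests on attribution and low cost, not on a demonstrated loss of power.

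**What to change.** 1. Define the ion subset as the first 15 patients per arm without another metal joint implant, established at screening before allocation is known.
2. Adjust the ion comparison for the preoperative value.
3. Record the date of any later metal implant. Keep all values in the intention-to-treat ion analysis, and add a sensitivity analysis restricted to samples taken before such an implant.
4. Reconcile the densitometry wording with eligibility: treat the opposite hip as a native reference only while it is unoperated.

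The cost is one screening question, one recorded date and one extra analysis. A few early patients would be passed over for the ion subset, and its results would apply to patients with a single prosthesis. The sensitivity analysis removes data after a post-randomisation event, so it should support the main analysis and not replace it.

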#### Serum metal ion concentration

Serum ion concentrations for cobalt, chromium and titanium will be determined by venous blood sampling. Cobalt and titanium concentrations are analyzed by inductively coupled plasma mass spectrometry (ICP-MS; Agilent 7500 series, Agilent Technologies) and chromium is measured by grafite furnace atomic absorption spectrometry with Zeeman correction (GFAAS; Varian 220Z, Varian Inc.). The patients' sera may also be used to assess cytokine levels and effects of these ions on osteoblast cells.

#### Perioperative measurements

Surgical approach, surgical time and intra-operative blood loss are recorded. Perioperative complications will be registered, including hip dislocations.

#### Self-reported and physician reported functional status and range of motion

The validated Oxford self-rating questionnaire will be used to assess self reported functional status [10]. The validated Harris Hip Score is used to assess patient and physician reported functional status, as well as range of motion [11,12].

#### Radiographic evaluation

During every follow-up visit standard supine anteroposterior (AP) pelvic hip radiographs (with 115% magnification) will be taken. The AP radiographs at 6 weeks will serve as baseline, and will be compared to the X-rays 5 years and 10 years postoperatively. Radiographs are reviewed for presence of femoral radiolucent lines and scored according to the 7 zones described by Gruen et al. [13]. Peri-acetabular radiolucencies are assessed according to the three zones of De Lee and Charnley [14]. The scoring will be undertaken by an independent reviewer.

### Sample size

It is our hypothesis that large head metal-on-metal arthroplasties will show less bone mineral density loss and higher serum metal ion concentrations compared to the conventional 28 mm metal-on-polyethylene articulations. In order to detect a least clinical relevant difference in bone mineral density (BMD) of 0.25 g/cm^2 ^with a standard deviation of 0.4, 41 patients are needed in each group (alpha 0.05, power 0.80). Based on previous work with cemented THA we expect a drop-out rate of 10%, but we also expect conversion to cemented cups if adequate cementless fixation fails. We therefore aim to include 50 patients in each group. Comparable studies also used 50 patients in each group [15,16]. In order to detect a clinical difference of 2.5 μg/liter in serum metal ion concentration with a standard deviation of 1.8, 8 patients per group are needed (alpha 0.05, power 0.80). To compensate for patients withdrawn from the study, (the first) 15 patients will be included in each group. A comparable study used 10 patients in each group [17].

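### The BMD sample size does not say whether 0.25 and SD 0.4 are a level or a change, and no reference scan is named for the hypothesised BMD loss

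*Protocol article*

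**What the plan says.** The Background section of the Protocol article hypothesises that "the large head metal-on-metal arthroplasties show less bone mineral density loss", and the Sample size section repeats this. Bone densitometry says that DEXA is performed "in order to calculate bone density changes around the acetabular component".

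The next sentence of Sample size then specifies a "least clinical relevant difference in bone mineral density (BMD) of 0.25" g/cm². It takes the SD as 0.4 and arrives at 41 per group, for a two-group comparison at the 0.05 level and 80% power. It gives no time point, region of interest or reference scan, and it does not identify the difference or the SD as one of change.

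The Measurements section sets one schedule for all outcomes: "Measurements will take place preoperatively, perioperatively, and postoperatively (6 weeks, 1 year, 5 years and 10 years"). Radiographic evaluation names the 6-week film as its baseline; Bone densitometry names none.

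Statistical analysis names no test for BMD. For Oxford and Harris scores, if skewed, it gives a Wilcoxon signed-rank test within groups and a Mann-Whitney test between groups. It mentions no adjustment for preoperative values.

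**The concern.** The hypothesis is about loss, and the quantity sized is an unlabelled difference in BMD. The number of patients needed for a level, for a change score and for a baseline-adjusted comparison can differ widely, so a reader cannot tell what the 41 per group delivers for the hypothesis.

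The choice of reference scan also matters in this trial. Before surgery there is no cup around which to place periprosthetic regions, and change from a preoperative scan would include bone removed in preparing the socket. The arms also put different metal in the scan field: a cobalt-chromium liner with a 38 to 60 mm head against a polyethylene liner with a 28 mm head. Any fixed measurement offset from this would cancel only in a change measured from a scan taken after implantation.

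Finally, measurements taken before surgery or early after it carry information that an unadjusted comparison of later values does not use.

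**Working it through.** **Inputs from the article:** difference 0.25 g/cm², SD 0.4, alpha 0.05, power 0.80 (Sample size); two-sided testing (Statistical analysis). **Assumed:** the correlation r between reference and follow-up BMD, which the article does not give, with equal variances at the two times. The range 0.3 to 0.8 is shown.

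**1. The plan's figure.** n per group = 2 × [SD × (1.960 + 0.842) / difference]² = 2 × [0.4 × 2.802 / 0.25]² = 40.19, rounded up to 41. By the noncentral t distribution, power at 41 per group is 0.798 and 42 would be needed. The figure reproduces as a two-sample comparison of means with no baseline term. This does not show that 0.4 is the SD of a level: the same formula gives 41 if 0.4 is the SD of a change.

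**2. If 0.4 is the SD of a level.**
- Baseline-adjusted SD (ANCOVA) = 0.4 × √(1 − r²); detectable difference ≈ 0.25 × √(1 − r²).
- Change-score SD = 0.4 × √(2(1 − r)); detectable difference ≈ 0.25 × √(2(1 − r)).

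n is by the normal formula in step 1, power by noncentral t at 41 per group, and detectable differences are at about 80% power with 41 per group.

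| r (assumed) | ANCOVA SD | n | power | detectable | Change SD | n | power | detectable |
|---|---|---|---|---|---|---|---|---|
| 0.3 | 0.382 | 37 | 0.834 | 0.24 | 0.473 | 57 | 0.656 | 0.30 |
| 0.5 | 0.346 | 31 | 0.898 | 0.22 | 0.400 | 41 | 0.798 | 0.25 |
| 0.7 | 0.286 | 21 | 0.975 | 0.18 | 0.310 | 25 | 0.950 | 0.19 |
| 0.8 | 0.240 | 15 | 0.997 | 0.15 | 0.253 | 17 | 0.993 | 0.16 |

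At r = 0, ANCOVA needs 41 per group and a change score 81. A plain change score therefore does worse than a comparison of levels below r = 0.5 and better above it.

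**3. If 0.4 is the SD of a change.** The 41 per group is right for a change score at any r. Adjustment still helps, but differently: the ratio of the ANCOVA SD to the change SD is √(1 − r²) / √(2(1 − r)) = √((1 + r)/2). The detectable difference becomes 0.25 × 0.806 = 0.20 at r = 0.3, 0.25 × 0.866 = 0.22 at 0.5, 0.25 × 0.922 = 0.23 at 0.7 and 0.25 × 0.949 = 0.24 at 0.8.

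**4. What each analysis does to a fixed implant offset d present in both postoperative scans.** A change score gives d − d = 0. ANCOVA with slope b leaves d(1 − b). With equal variances b = r, so 70%, 50%, 30% and 20% of d remain at r = 0.3, 0.5, 0.7 and 0.8. The documents give no size for d.

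**The case against.** The strongest reply is that much of this is silence in a condensed article. The reference scan and covariates are details that a full protocol or analysis plan commonly holds, perioperative and 6-week measurements are listed, and DEXA is said to serve the calculation of changes. The 0.25 and 0.4 directly follow the hypothesis about loss and may well describe change, in which case 41 per group is correct. This stands. A reader might infer that the trial is sized on raw levels, or that no postoperative baseline will be used; the article states neither.

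A reader might also infer that implant or socket-preparation effects will be mistaken for bone loss. That needs a comparison of raw levels or a preoperative reference, and neither is stated as the plan. Metal removal software and a control region in the ilium are specified. Differential bone removal is not shown either. For the metal-on-metal arm, "The geometry of the patient determines the largest possible shell size and head size to be implanted", but no shell sizing rule is given for the other arm to compare with it.

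It is also fair to say that omitting ANCOVA is not an error, that its gain depends on an unstated correlation, and that adjusting for a scan taken after randomisation does not remove an implant offset (step 4 of the working). The power figures for ANCOVA further assume that the arms are similar on that scan, which randomisation does not guarantee once the implant is in place.

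The reply does not remove the point that the article itself states a sample size whose two inputs are not tied to the hypothesised quantity, and that it names a baseline for a secondary outcome but not for this primary one.

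**Conclusion.** The point holds as a request to define the BMD outcome and as a cheap gain in precision. It does not show a faulty calculation or a biased plan. The 41 per group is correct for its stated inputs, but whether it is right for BMD loss depends on what 0.4 describes. If it is the SD of a change, 41 stands. If it is the SD of a level, a change score needs 57 per group at r = 0.3, 41 at 0.5 and 25 at 0.7.

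If 0.4 is the SD of a level, baseline adjustment gives power of 0.83 to 0.997 at 41 per group for r from 0.3 to 0.8, against 0.80 unadjusted, and it does not materially lose power at any r. These figures rest on the assumed correlation, equal variances, and arms balanced on the covariate. Bias from the implants or from preparing the socket remains conditional on a comparison that the article does not describe.

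**What to change.** 1. Define the primary BMD outcome as change from the first DEXA after implantation (the perioperative scan if taken once the cup is in place, otherwise 6 weeks), in the same regions of interest, at a named time point. Any fixed implant offset then cancels.
2. Report a baseline-adjusted estimate (ANCOVA, or a mixed model over visits) alongside it, noting that adjustment on a post-randomisation scan leaves part of any between-arm offset.
3. State whether SD 0.4 is for level or change, and restate the detectable difference. If it is for level and ANCOVA is used, this is about 0.24, 0.22, 0.18 and 0.15 g/cm² at 41 per group for assumed correlations of 0.3, 0.5, 0.7 and 0.8.
4. Adjust the ion, Oxford and Harris comparisons for their preoperative values, rank-based if skewed. Those values precede implantation, so the offset problem does not arise.

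The cost is wording. No patients are added, and no scans are added provided that the general visit schedule applies to DEXA, which the article does not spell out. There are two downsides: bone lost before the reference scan falls outside the estimate, and a plain change score loses power against a comparison of levels if the correlation is below 0.5.
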